** to be filled in after edits **

**A. SPECIFIC AIMS___________________________________________________________________________**

*List the broad, long-term objectives and the goal of the specific research proposed, e.g., to test a stated hypothesis, create a novel design, solve a specific problem, challenge an existing paradigm or clinical practice, address a critical barrier to progress in the field, or develop new technology.*

This study is a clinical trial investigating exposure of Mozart's Sonata for Two Pianos in D Major (hereafter K448) to a large cohort of pediatric and adult individuals with special needs, many of whom have epilepsy, who reside at the Thad E. Saleeby Center in Hartsville, SC. All individuals at the Thad E. Saleeby Center will participate in the study assuming completion of appropriate inclusion criteria, IRB approval from MUSC/MUHA and DDSN, and appropriate consent completion.

The specific aim of this study is to determine if exposure to K448 decreases seizure frequency in neurologically-impaired individuals. Detailed seizure-reporting is standard protocol at the Saleeby Center and therefore baseline data has been accumulated for the previous 4 years, making for long-term accumulation of pre- and post-exposure data analysis.

Secondary outcome measures will be collected, including (1) sleep patterns, (2) neurobehavioral dysfunction, and (3) other seizure characteristics. These outcome measures will be collected according to the standard recording procedures currently in place at the Saleeby Center, but will be extended to include all individuals.

**B. BACKGROUND AND SIGNIFICANCE_________________________________________________________**

*Briefly sketch the background leading to the present application, critically evaluate existing knowledge, and specifically identify the gaps that the project is intended to fill. State concisely the importance and health relevance of the research described in this protocol by relating the specific aims to the broad, long-term objectives. If the aims of the study are achieved, state how scientific knowledge or clinical practice will be advanced.*

Epilepsy is a world-wide disorder effecting all age and ethnic groups with substantial impact on quality of life, morbidity, and mortality. Current treatments focus on amelioration of symptoms, e.g. decreased seizures, but fail in curing epilepsy. Research is increasingly focusing on this goal of curing epilepsy. Finding safe, non-invasive methods of decreasing seizures, and potentially reversing the epileptogenic process, is of paramount importance in improving the lives of those with epilepsy.

**This study focuses on a specific and safe method of attempting to alter seizure frequency in persons with epilepsy. The generalized Mozart effect has documented short- and long-term effects in brain functioning, including decrease in seizures and epileptiform discharges (Turner 2004, Hughes 2001). The generalized Mozart effect has only been described within the last 15 years, and consists of enhanced or normalized higher brain function in response to exposure to music.**

**This effect was first published in the seminal study by Rauscher and colleagues (1993) who demonstrated enhanced spatial-temporal (ST) reasoning in a cohort of college students exposed to the Mozart Sonata for Two Pianos in D Major, K. 448 (hereafter K448). Patterned stimulation, exemplified in the Generalized Mozart effect, was initially studied in the 1980’s by Leng, McGrann, and Shaw who demonstrated reversal of the epileptic state based on the mathematical trion model of Mountcastle’s columnar organization of the mammalian neocortex. This ultimately led to demonstration of decreased seizures and interictal epileptiform discharges (IEDs) by Hughes in the 1990’s. Hughes work is currently being extended to systematic studies of the Generalized Mozart effect on the human EEG and IEDs (Turner 2004). The generalized Mozart effect has also been exhibited in animal models. A recent study at the M.I.N.D. Institute reveals enhanced spatial maze learning in rats exposed to K448 (Aoun in press).**

**Ideally, the proposed study will put a novel stimulus for studying epilepsy to the rigors of scientific testing using a large cohort of subjects. This method of exposure to K448, if effective, could lead to a new understanding of epilepsy and perhaps result in new forms of non-invasive seizure management.**

**C. PRELIMINARY STUDIES___________________________________________________________________**

*Provide an account of the principal investigator’s preliminary studies pertinent to this protocol and/or any other information that will help to establish the experience and competence of the investigator to pursue the proposed project.*

The principle investigator has conducted two preliminary studies for this project. The first, published in Epilepsy and Behavior, was a randomized, single-blinded, crossover, placebo-controlled, clinical trial investigating the effect of Mozart's Sonata for Two Pianos (K448) on the frequency of interictal epileptiform discharges (IEDs) in EEGs of children with benign childhood epilepsy. Two of the four subjects in the pilot study demonstrated sufficient waking IEDs for statistical analysis. Significant decreases in IEDs per minute (33.7, 50.6 and 33.9%) were demonstrated when comparing baseline with exposure to K448, but not to control music (Beethoven's Fur Elise).

**The second study was expanded to include ten children with rolandic epilepsy. Twelve hours of sleeping EEG were recorded for each child while Mozart and Beethoven alternated quietly in the background. The data is currently undergoing Independent Component Analysis (ICA) to statistically compare the three conditions: silence (baseline), Mozart and Beethoven (control). Preliminary results indicate that sleep patterns were not disturbed by the background music.**

**D. RESEARCH DESIGN AND METHODS (including data analysis) __________________________________**

*Describe the research design and the procedures to be used to accomplish the specific aims of the project. Include how the data will be collected, analyzed, and interpreted and specify what statistical methods will be used. Describe any new methodology and its advantage over existing methodologies. Discuss the potential difficulties and limitations of the proposed procedures and alternative approaches to achieve the aims. As part of this section, provide a tentative sequence or time-table for the project. Point out any procedures, situations, or materials that may be hazardous to personnel and the precautions to be exercised.*

Study Subjects: Individuals at the Thad E. Saleeby Center are all candidates for participation in this study. The ages will range from 5 to 90 years old.

Inclusion criteria:

• Resident of the Thad E. Saleeby Center

• Epilepsy or seizure disorder

• At least one year of detailed seizure reporting prior to study starting date

Exclusion criteria:

• Severe hearing impairment

Written informed consent will be obtained for all participants. If an individual is not capable of giving informed consent, a parent or legal guardian will be asked to act in the best interest of the patient in accordance with DDSN Departmental Directive 535-07-PD (see consent form for more details).

Children and adults who have given informed consent to participate in this study will be randomized into two groups: Group 1 (2/3 of participants) will be exposed to Mozart music at night and Group 2 (1/3 of participants) will be exposed to silence at night. Special care will be taken to make sure the audio levels for Group 1 do not disrupt their sleep cycles. Preliminary data from a pilot study at MUSC shows that background music does not alter sleep patterns.

Group 1 Protocol: Exposure to K448 will occur nightly between the hours of 9:00 p.m. and 7:00 a.m. Each room will have a sound system installed in it to deliver the stimuli. The stimuli will be presented in the same pattern as the 2002 ten-subject pilot study at MUSC:

Pre-exposure: The first 9 minutes of each hour will be silent.

Exposure: 8.5 minutes of K448 will follow the silent baseline.

Post-exposure: 8.5 minutes of silence will follow K448 acting as a washout.

The exposure and post-exposure epochs will play 3 times each hour before the cycle repeats the following hour beginning with another 9 minute baseline. Since the cycle is exactly 60 minutes in length, we will be able to deliver the entire stimulus train on one 80-minute compact disk from a central location in the Saleeby Center.

Group 2 Protocol: No music will be played for the control group. Evening and morning routines for both groups should remain identical.

Data Collection: A tentative start date for the project is January 1, 2006. Prior to this date, it is important to outline what data will be collected. The primary outcome measure for the study is seizure frequency. Therefore detailed records of seizure frequency by the Saleeby staff will be critical to quantifying any significant changes compared to baseline (previous years). Duration and intensity of seizures would also be useful as secondary measures of outcome in addition to sleep patterns and behavior.

Data will be collected on each individual for each outcome measure during the 12 month period of exposure. Interim analyses will occur monthly, quarterly, and at 6 months into the study.

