*- Provide information about how the specimens, records, or data are collected and whether material or data will be collected specifically for your proposed research project.*

The researchers working on this study will analyze the clinical information that is already routinely collected on the individuals at the Saleeby Center. This information includes observed seizures, sleep patterns and behavior. The researchers may also collect other information including the individuals medications as well as pretinent baseline information collected during the time prior to the study (e.g., seizure frequency, sleep patterns, behavior).

All of the data will be associated with a non-identifying number in place of the subject's name. Physical data will be locked up and electronic data will be password-protected. Only members of the research team will have access to this information.

c. Potential Risks

*- Describe the potential risks to subjects (physical, psychological, social, legal, or other), and assess their likelihood and seriousness to the subjects.*

*- Where appropriate, describe alternative treatments and procedures, including the risks and benefits of the alternative treatments and procedures to participants in the proposed research.*

There are minimal risks involved with this study. There is a slight chance that the music might disrupt a subject's sleep patterns. To prevent this from happening, the volume level of the Mozart music will be adjusted so that it does not wake them up or prevent them from falling asleep. Preliminary research at the Medical University of South Carolina by the principle investigator has shown that the music exposure does not affect a subject's sleep cycle.

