4. IMPORTANCE OF THE KNOWLEDGE TO BE GAINED

*- Discuss the importance of the knowledge gained or to be gained as a result of the proposed research.*

*- Discuss why the risks to subjects are reasonable in relation to the importance of the knowledge that reasonably may be expected to result.*

*- NOTE: Test articles (investigational new drugs, devices, or biologicals) including test articles that will be used for purposes or administered by routes that have not been approved for general use by the Food and Drug Administration (FDA) must be named. State whether the 30-day interval between submission of applicant certification to the FDA and its response has elapsed or has been waived and/or whether use of the test article has been withheld or restricted by the Food and Drug Administration, and/or the status of requests for an IND or IDE covering the proposed use of the test article in the research plan.*

The risk/benefit assessment for this project is excellent. The subjects are exposed to no more than minimal risk and the results, if valid, represent a significant non-invasive treatment for reducing seizure frequency, improving sleep patterns and reducing behavioral problems. Joining the research project is completely optional and if a subject joins and later decides to leave the study, they may do so without fear of penalty or loss of benefits.

5. SUBJECT SAFETY AND MINIMIZING RISKS (Data and Safety Monitoring Plan)

*Studies that involve *clinical trials (see description below) must include a description of the plan for subject safety and minimizing risks of the research, including data monitoring and adverse event reporting to ensure the safety of subjects. The complexity of the plan should be determined by the level of risk to subjects. The plan should specify: 1) what will be monitored, 2) how frequently the monitoring will occur, 3) who will be responsible for the monitoring, and 4) study endpoints.*

Data and safety monitoring will be the responsibility of the principle investigator ([name]) and the Co-directors of the Thad E. Saleeby Center ([name] and [name]).

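### Eligibility does not screen for seizures recorded as triggered by sound or music, and the risk section does not name a possible increase in seizures

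*Protocol*

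**What the plan says.** **Eligibility (Section D).** Every resident is a candidate: "Individuals at the Thad E. Saleeby Center are all candidates for participation in this study". There are three inclusion criteria: residence at the Center, "Epilepsy or seizure disorder", and "At least one year of detailed seizure reporting prior to study starting date". The exclusion list has one entry: "Severe hearing impairment". No criterion refers to seizure type or trigger. The year of records is an entry requirement and a baseline; nothing says it is read for triggers before randomisation.

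**Exposure (Section D).** "Group 1 (2/3 of participants) will be exposed to Mozart music at night"; the remaining third have silence. "Exposure to K448 will occur nightly between the hours of 9:00 p.m. and 7:00 a.m". Each hourly cycle contains three plays of 8.5 minutes, and exposure lasts 12 months.

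**Risk.** Section E.1.c, Potential Risks, says: "There is a slight chance that the music might disrupt a subject's sleep patterns". It names no other risk. Section E.2.b repeats the sleep risk and adds confidentiality of health information, which is not a risk of the music. Section E.4 concludes: "The subjects are exposed to no more than minimal risk".

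**Safeguards.** Sections E.1.c and E.2.b have the music played quietly, at a volume adjusted to each person. Section E.5 puts seizure frequency first among the things monitored, with observation day and night. Section D adds monthly, quarterly and six-month interim analyses.

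**The concern.** The music is given because it may change how often seizures occur (Section B), and everyone enrolled has a seizure disorder. The one auditory criterion removes people who cannot hear the stimulus. It does not remove anyone whose record shows sound to be a trigger.

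The account of effects also runs one way. Section E.3 offers fewer seizures as the main potential benefit, but no section considers that seizures might increase in some residents. An intervention tested for its effect on seizure frequency cannot be assumed to move it only downwards.

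What is at stake is avoidable exposure of a possible few residents, and a complete risk statement for those who decide on their behalf. Section E.2.a says that most residents cannot consent for themselves, so parents or guardians rely on what the protocol and consent form tell them.

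**Working it through.** The protocol gives no statistical figure on this point to reproduce. The check compares the text of several sections and adds simple arithmetic on the schedule.

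**1. Does a resident with a recorded sound trigger meet every criterion?**
- Resident of the Center: yes.
- Epilepsy or seizure disorder: yes, since type and trigger are not restricted.
- One year of detailed seizure records: yes, by supposition.
- Severe hearing impairment: no.

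Such a resident is eligible, and the probability of the music group is 2/3.

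**2. How much exposure follows?** (Section D)
- Cycle length: 9 + 3 × (8.5 + 8.5) = 60 minutes, which agrees with the protocol's own statement of the cycle.
- Plays per night: 3 per hour × 10 hours = 30.
- Music per night: 3 × 8.5 × 10 = 255 minutes, or 4.25 hours.
- Plays per year: 30 × 365 = 10,950.
- Hours per year: 4.25 × 365 ≈ 1,551.

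These figures measure exposure, not harm.

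**3. How many residents could be affected?** The documents give no number. For illustration only, assume n between 0 and 3 among the 85 to 92 residents in Section H. The expected number given music is 2n/3, so between 0 and 2. If all residents were eligible and consented, which is an upper bound, the music group would be 2/3 × 85 ≈ 57 to 2/3 × 92 ≈ 61 people.

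**4. Is a seizure increase named as a risk anywhere?**

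| Section | Effects named |
| --- | --- |
| B | Music intended to change seizure frequency |
| E.1.c | Disturbed sleep |
| E.2.b | Disturbed sleep; confidentiality |
| E.3 | Fewer seizures; possible gain in sleep and behaviour |
| E.4 | Risk no more than minimal |
| E.5 | Seizure frequency monitored as the primary outcome |

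No section names more frequent or provoked seizures as a possible harm.

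**5. Do the pilot studies in Section C settle it?** No. One had four children with benign childhood epilepsy, two of them analysable. The other had ten children with rolandic epilepsy, whose discharge data were still being analysed. The reassurance taken from the second concerns sleep. The present trial admits ages 5 to 90 with any seizure disorder.

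**The case against.** The strongest reply is that the affected resident is hypothetical. The protocol never mentions seizures triggered by sound or music, and what it reports about K448 points to fewer seizures and discharges. It describes a detailed log of seizure events but does not say that triggers are noted. That stands, and it limits the weight of the point. It does not remove it: the proposed criterion acts only where the Center's own records show the trigger, so it excludes nobody if there is no such resident.

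The second reply is that safeguards exist. Low, individually adjusted volume makes startle less likely, and round-the-clock recording means that worsening would be noticed. This also stands in part. The volume control is aimed at sleep, and no action is attached to a rise in one person's seizures. Neither changes who may enter or what the risk section says.

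A reader might make two stronger inferences, and the documents support neither:
- **That such residents have to be enrolled.** Meeting the criteria makes someone a candidate only. Participation depends on IRB and state agency approval (Section A) and on consent, with a parent or guardian acting in the resident's interest where needed (Section D). Joining is voluntary and withdrawal is free (Section E.4).
- **That these residents would mask a benefit or bias the primary comparison.** No seizure rate or number of affected residents is given, and the protocol does not fix a comparison of group means. X extra seizures in one resident would move the mean of 57 to 61 people by X/57 to X/61, but X is unknown.

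The consent form is not in the text under review and may already name further risks.

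**Conclusion.** The point holds as a low-frequency safety and disclosure gap. As written, a resident with documented sound- or music-triggered seizures is eligible and has a 2/3 chance of about 10,950 plays over the year. The only risk of the music named in Section E.1.c is disturbed sleep.

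The eligibility part is conditional on such a resident existing and on the records noting triggers; the number may be zero. The disclosure part does not depend on either: the risk statement omits the unfavourable direction of the outcome that the music is meant to change. No effect on the primary result is shown. The gap is worth closing because doing so is cheap, but confidence that anyone is actually affected is low.

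**What to change.** 1. In Section D, add to the exclusion criteria: seizures documented in the Center's records as triggered by music or sound. State that this is checked, before randomisation, against the year of seizure records already required for entry.
2. In Section E.1.c, name a possible increase in seizures as a risk of the music, and bring Sections E.2.b and E.4 into line with it.
3. Add the same risk to the consent form if it is not already there.

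The cost is one review of records already held and a few sentences of text. The downside is the possible loss of a few residents and slightly narrower generalisability. If the records turn out not to note triggers, the criterion will exclude nobody and the protocol should say so; the risk wording is still needed.

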2. ADEQUACY OF PROTECTION AGAINST RISKS

a. Recruitment and Informed Consent

*- Describe plans for the recruitment of subjects (where appropriate) and the process for obtaining informed consent. If the proposed studies will include children, describe the process for meeting requirements for parental permission and child assent.*

*- Include a description of the circumstances under which consent will be sought and obtained, who will seek it, the nature of the information to be provided to prospective subjects, and the method of documenting consent.*

Participants will be recruited from the current residents of the Thad E. Saleeby Center. Informed consent will obtained by the principle investigator, [name]. Since the majority of the individuals are unable to give informed consent, special language has been included in the consent form for the parent/legal guardian acting on the individual’s behalf in accordance with the South Carolina Department of Disabilities and Special Needs (Form 535-07-PD).

b. Protection against Risk

- *Describe planned procedures for protecting against or minimizing potential risks, including risks to confidentiality, and assess their likely effectiveness.*

*- Where appropriate, discuss plans for ensuring necessary medical or professional intervention in the event of adverse effects to the subjects.*

*- Studies that involve clinical trials (biomedical and behavioral intervention studies) must include a description of the plan for data and safety monitoring of the research and adverse event reporting to ensure the safety of subjects in Section 4 below.*

The only change from normal care that is being proposed is that Mozart music will be quietly played in the background in one group of individuals. The data collection that will yeild the primary and secondary outcome measures is the same protocol that is already in place at the Saleeby Center. One possible risk is that an individual's sleep patterns may be distrubed. Preliminary studies at the Medical University of South Carolina by the principle investigator have shown that sleep cycles are not altered by the music. Special care will be taken to tailor the volume threshold on a patient-to-patient basis.

The risk of compromising protected health information (PHI) will be minimized by locking up physical medical records and password-protecting computer records. Only staff at the Thad E. Saleeby Center and members of the research team will have access to the research files.

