**5(5):662-8.**

G. CONSULTANTS__________________________________________________________________________

*Where applicable, attach electronic versions of appropriate letters from all individuals confirming their roles in the project. Go to the application under “additional uploads” to attach this information*.

H. FACILITES AVAILABLE____________________________________________________________________

*Describe the facilities available for this project including laboratories, clinical resources, etc.*

The Thad E. Saleeby Center is a state-run facility operating under the South Carolina Department of Disabilities and Special Needs. The Saleeby Center is a permanent residence home for individuals with specials needs and disabilities who require assisted living. There are fifty-five 2-patient bedrooms divided among three wings of the facility. There are also 14 unique day rooms that are specifically designed for different tasks including reading, arts and crafts, physical therapy, etc. The Co-directors of the Saleeby Center stress a high level of care tailored specifically to each individual’s unique needs. There are currently 85-92 individuals residing at the Saleeby Center, most of whom have epilepsy or a seizure-related disorder and might benefit from this research study.

I. INVESTIGATOR BROCHURE ____________________________________________________

*If applicable, attach the electronic version of the investigator brochure. Go to the application under “additional uploads” to attach this information.*

J. APPENDIX_______________________________________________________________________________

*Attach any additional information pertinent to the application, such as surveys or questionnaires, diaries or logs, etc. Go to the application under “additional uploads” to attach this information.*

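### Participants are randomised one by one, but the music is delivered by room in two-patient bedrooms, and nothing keeps roommates in the same arm

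*Protocol*

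**What the plan says.** Protocol Section D, Study Subjects, sets the allocation: "Children and adults who have given informed consent to participate in this study will be randomized into two groups". The split is 2:1: "Group 1 (2/3 of participants) will be exposed to Mozart music at night", while the remaining third is assigned to silence. No room, wing or roommate pair is named as the unit.

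The Group 1 Protocol in the same section sets the delivery: "Each room will have a sound system installed in it to deliver the stimuli". The plan is to "deliver the entire stimulus train on one 80-minute compact disk from a central location in the Saleeby Center". Section E.2.b describes soft background music; headphones or other personal playback are not mentioned. It adds: "Special care will be taken to tailor the volume threshold on a patient-to-patient basis".

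The Group 2 Protocol promises: "No music will be played for the control group".

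Section H describes the building: "There are fifty-five 2-patient bedrooms divided among three wings of the facility". It gives the current population as 85-92 residents and says that most have epilepsy or a related disorder. The planned-enrolment table in Section E.1.a is empty.

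**The concern.** These statements cannot all hold in a room shared by a Group 1 and a Group 2 participant. A control in such a room hears whatever the room system plays. No passage says that roommates go to the same arm, that residents are moved, or that mixed rooms are avoided.

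The randomised comparison of seizure frequency is what is at stake. Exposed controls pull the two arms together and bias a true effect towards zero. The between-arm comparison of sleep, which covers the one physical risk the protocol names, is diluted in the same way. Analysis cannot restore a silent control arm that was not silent, so this belongs in the protocol and cannot be left to the statistical analysis plan.

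Two further conflicts follow from the same mechanism:
- A resident who has not joined, but shares with a Group 1 participant, would be exposed nightly for a year, although Section E.4 describes joining as voluntary.
- Volume set patient by patient is hard to reconcile with one system serving two occupants.

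**Working it through.** The protocol gives no contamination figure, sample size or power, so there is no figure of its own to reproduce.

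**Inputs from the protocol.** R = 55 two-bed rooms and N = 85 to 92 residents (Section H); 2/3 of participants to music (Section D).

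**Assumptions.** q, the share of residents enrolled; how residents are spread over rooms; roommates allocated independently.

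**Step 1: how many residents share.** Sharing is least when every room is used. The number of shared rooms is then N - 55.
- N = 85: 30 shared rooms, 60/85 = 71% of residents share.
- N = 92: 37 shared rooms, 74/92 = 80% share.
- If rooms are filled in pairs: 84/85 = 99% and 92/92 = 100%.

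**Step 2: chance that a control has a Mozart roommate.** c = P(has a roommate) × n1/(N - 1), where n1 is the number assigned to music.

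| Enrolled share | N | Music : silence | n1/(N - 1) | c, maximum spread | c, all paired |
|---|---|---|---|---|---|
| 100% | 85 | 57 : 28 | 57/84 = 0.679 | 0.479 | 0.671 |
| 100% | 92 | 61 : 31 | 61/91 = 0.670 | 0.539 | 0.670 |
| 60% | 85 | 34 : 17 | 34/84 = 0.405 | 0.286 | 0.400 |
| 60% | 92 | 37 : 18 | 37/91 = 0.407 | 0.327 | 0.407 |
| 51% | 85 | 29 : 14 | 29/84 = 0.345 | 0.244 | 0.341 |
| 51% | 92 | 31 : 16 | 31/91 = 0.341 | 0.274 | 0.341 |

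A simulation of 20,000 allocations at full enrolment and maximum spread gave 0.479 (N = 85) and 0.539 (N = 92), in agreement with the formula. In head counts, full enrolment exposes about 13 to 19 of 28 controls, or 17 to 21 of 31.

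**Step 3: what an exposed control hears.** The hourly cycle is 9 + 3 × (8.5 + 8.5) = 60 minutes, of which 3 × 8.5 = 25.5 minutes are music, from 9 p.m. to 7 a.m. A control in a mixed room gets the same schedule as the Group 1 roommate.

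**Step 4: dilution.** If exposure through a roommate has the full effect (assumption), the between-arm effect is (1 - c) of its true size. This is 1 - 0.24 = 76% at the low end of the table and 1 - 0.67 = 33% at the high end.

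**Step 5: the alternative.** With the bedroom as the unit, roommate exposure of controls is zero by construction, leaving aside sound through walls. With at most two participants per cluster the design effect is at most 1 + ICC: 1.05, 1.10 and 1.20 for assumed ICCs of 0.05, 0.10 and 0.20.

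**The case against.** The strongest reply is that the conflict is inferred. The allocation sentence does not forbid assigning roommates together, and the sentence on room systems stands under the Group 1 Protocol, so it need not mean that control rooms are wired. Both points are fair, but neither protects controls. The plain reading is allocation of persons, and a mixed room is a Group 1 room for the occupant assigned to music.

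The second reply concerns size, and it stands. A reader might take half to two-thirds of controls exposed as the expected result. That needs almost every resident to enrol. Section D requires epilepsy or a seizure disorder, a year of seizure records, no severe hearing impairment, and consent. A roommate outside the study brings no music. The exposed share therefore depends on an enrolment figure that the protocol leaves blank.

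Other stronger inferences are also unsupported:
- Controls do not hear music all night: the schedule has 25.5 minutes of music in each hour.
- A null result would be weakened but not emptied of meaning. The planned comparison with each person's earlier years is not contaminated within Group 1, although it is not a randomised contrast.
- Patient-level volume is not ruled out everywhere. It is in doubt only in shared rooms, and at maximum spread 20%-29% of residents sleep alone.
- Turning the dilution into a multiple of the required sample size has no anchor, since the protocol states no sample size or power and the pool is capped at 85-92.
- The protocol nowhere proposes allocating whole wings, so it cannot be faulted for that.

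**Conclusion.** The defect holds. Individual randomisation, room-level playback and two-patient bedrooms cannot together deliver the silence promised to controls, and no passage resolves this.

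Its size is conditional. The expected share of exposed controls is 48%-67% if nearly all residents enrol and roughly a quarter to 40% if 51%-60% enrol. It would be lower still if consent or the other criteria cut enrolment below that. The matching between-arm effect is about 33%-76% of its true size. These figures rest on independent allocation of roommates, on the assumed enrolment and room occupancy, and on roommate exposure acting like assigned exposure. Even at the low end, about a quarter of the contrast is lost, and a closed pool of residents leaves little room to make that up by recruiting.

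**What to change.** In Section D, make the bedroom the unit of randomisation, so that both occupants share an arm, preferably stratified by wing. The 2:1 ratio would then apply to rooms and hold only approximately for participants.

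Before allocation, establish which rooms could go to either arm: those with a single occupant, those where both occupants participate, and those where a non-participating roommate's agreement to exposure has been obtained. Randomise only those rooms. Never send a room to silence afterwards because a roommate did not agree, since arm would then depend on consent. Log room moves during the year, and allow for bedroom clustering in the analysis. Reconcile the patient-by-patient volume statement in Section E.2.b with shared rooms.

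The change needs new protocol wording and a room-based allocation list before the start. The statistical cost is a design effect of at most 1+ICC (1.05-1.20 for assumed ICCs of 0.05-0.20). The larger cost may be participants whose room cannot be cleared for either arm. At an assumed 60% enrolment, 29% (0.706 × 34/84) to 41% (1.0 × 37/91) of participants would have a non-participating roommate, and those whose roommate does not agree would be lost.
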